#### Quality of life

2.5.4

Quality of life is measured using the EQ-5D-5L and SF-36 questionnaires at baseline, 6 months, 12 months and 24 months. The EQ-5D-5L is a validated and extensively used tool to measure Quality of Life [30]. This questionnaire is divided in 5 dimensions: mobility, self-care, usual activities, pain/discomfort and anxiety/depression. Additionally, general quality of life is visually assed with a visual analog scale. The SF-36 is a set of questions relying on patient self-reporting [[31], [32], [33]].This tool comprises of questions relating to physical functioning, social functioning, mental health, energy, pain and perception of health.

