### Sample size calculation

2.6

For our primary outcome of ulcer recurrence, we estimate 8% recurrence in 12 months in the intervention group. This is a slightly conservative estimate, given the 11% ulcer recurrence in 53 subjects during 93 weeks of follow-up following needle tenotomy as reported by Hedegaard Andersen and colleagues [20]. In the control group, we estimate 36% ulcer recurrence in 12 months. This is slightly more positive compared to the 40% ulcer recurrence in 12 months seen in a recent review [10], and similar to the ulcer recurrence in the control group of a recently completed RCT by these authors [35]. With 8% ulcer recurrence in the intervention group and 36% in the control group, power 0.8, alpha 0.05, 1:1 randomization and intention-to-treat analysis, a total of 66 participants (33 per group) are required.

For our predefined secondary outcome of barefoot peak pressure, we estimate average barefoot peak pressure at the target toe of 400 kPa (standard deviation (SD): 250) in the control group and 180 kPa (SD: 100) in the intervention group following tenotomy. These estimates are based on clinical pilot data from our gait lab, with slightly more conservative estimates than found in our pilot study. With power 0.8, alpha 0.05, 1:1 randomization and intention-to-treat analysis, a total 40 participants (20 per group) are required for this predefined secondary outcome. With this number smaller than required for our primary outcome, the RCT can also be considered adequately powered for this outcome. The calculations were performed using clincalc.com [36].

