### Statistical analysis

2.7

Statistical analysis will be performed using SPSS. The Shapiro-Wilk W test will be used to determine the distribution. Continuous variables will be expressed as mean ± SD for normally distributed data and as median and interquartile range for not normally distributed and ordinal data. Shapiro-Wilk test and visual inspection will be performed to check for normality. In case of small sample sizes and when data is not normally distributed, Wilcoxon signed rank test will be used. Differences between groups will be compared using Fisher's Exact test or Kruskal-Wallis. A level of p < 0.05 is considered statistically significant.

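### The only between-arm test named for pressure, joint angles and quality of life takes no baseline covariate, although baseline is collected for all of them; the test is valid but less efficient than it need be

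*Protocol article*

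**What the plan says.** Section 2.7 (Statistical analysis) gives one sentence on comparisons between arms: "Differences between groups will be compared using Fisher's Exact test or Kruskal-Wallis". Fisher's exact test is for categorical outcomes, so continuous and ordinal outcomes fall to Kruskal-Wallis. The same section also states: "In case of small sample sizes and when data is not normally distributed, Wilcoxon signed rank test will be used". That is a paired test. The threshold is: "A level of p < 0.05 is considered statistically significant". No covariate, analysis of covariance or mixed model is named anywhere in the article.

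Baseline values exist for all the outcomes concerned. Table 1 marks barefoot pressure and weight-bearing CT at time 0, 6 and 12 months. Section 2.5.4 says: "Quality of life is measured using the EQ-5D-5L and SF-36 questionnaires at baseline, 6 months, 12 months and 24 months".

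Section 2.6 sizes the pressure outcome on "average barefoot peak pressure at the target toe of 400 kPa (standard deviation (SD): 250) in the control group and 180 kPa (SD: 100"), and concludes that "a total 40 participants (20 per group) are required for this predefined secondary outcome". The trial size comes from the primary outcome: "a total of 66 participants (33 per group) are required".

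**The concern.** The trial is small, and it measures each of these outcomes before treatment and at two or three visits afterwards. When a baseline value predicts the follow-up value, putting it in the between-arm model removes variance that has nothing to do with treatment. Kruskal-Wallis cannot do this. It also handles one visit at a time and returns a p-value with no between-arm difference and no interval.

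What is at stake is how precisely the secondary objectives in section 2.1 are answered. Joint angles and quality of life are the most exposed, because the article gives no power calculation for them. This is a stated choice of test, so it goes beyond detail that a condensed article leaves to a fuller document: an analysis plan that adjusted for baseline would depart from the published text.

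**Working it through.** **Inputs from the article (sections 2.6 and 2.7).** 33 per arm; power 0.80; alpha 0.05 (two-sided assumed); pressure means 400 and 180 kPa, difference 220 kPa, SDs 250 and 100. The baseline/follow-up correlation r is not given, so 0.3, 0.5 and 0.7 are assumed.

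**Step 1: the plan's own pressure figure.** For an unadjusted comparison of two means with common SD 250, n per group = 2 × (250 × (1.960 + 0.842) / 220)² = 20.3, rounded up to 21 (42 in total). The stated 20 per group (40 in total) is within rounding of this; power at 20 per group is 0.795. Using both stated SDs gives (250² + 100²) × 2.802² / 220² = 11.8, so 12 per group, which does not match. The stated figure is therefore an unadjusted comparison with SD 250 in both arms.

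**Step 2: pressure power at the trial size.** At 33 per arm the unadjusted power is 0.95 with SD 250. With the two stated SDs (root mean square 190.4) it is above 0.99.

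**Step 3: what baseline adjustment would gain.** Set the common outcome variance to 1.

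- Follow-up values alone: variance 1. Baseline-adjusted: 1 − r². Ratio: 1 − r².
- Change scores: variance 2(1 − r). Ratio: (1 − r²) / (2(1 − r)) = (1 + r)/2.

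The equivalent number per arm is 33 divided by the ratio.

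| Assumed r | Ratio against follow-up values | 33 per arm works like | Ratio against change scores | 33 per arm works like |
|---|---|---|---|---|
| 0.3 | 0.91 | 36 | 0.65 | 51 |
| 0.5 | 0.75 | 44 | 0.75 | 44 |
| 0.7 | 0.51 | 65 | 0.85 | 39 |

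These ratios hold for linear models with equal variances and a common baseline slope. Applied to a rank test they are approximate.

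**Step 4: direct check by simulation.** 33 per arm, normal data, true effect 0.5 SD, 4,000 runs, power at p < 0.05:

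| Assumed r | Kruskal-Wallis, follow-up values | Kruskal-Wallis, change scores | Baseline-adjusted linear model |
|---|---|---|---|
| 0.3 | 0.49 | 0.38 | 0.55 |
| 0.5 | 0.49 | 0.49 | 0.63 |
| 0.7 | 0.51 | 0.71 | 0.80 |

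The adjusted model does best in every row. A small part of its advantage comes from using normal data: the unadjusted normal-theory power is 0.53, slightly above Kruskal-Wallis on follow-up values. The rest comes from baseline.

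**The case against.** The strongest reply is that the article does not say what Kruskal-Wallis will be applied to. Section 2.1 words the secondary objectives as musculoskeletal and biomechanical changes, and the abstract speaks of assessment before and after the intervention. Ranking change scores would fit the text and would use baseline. **This stands.** It is wrong to say flatly that baseline will be ignored, and wrong to take 65 per arm as the headline figure, because at r = 0.7 the change-score reading gives 39. It does not remove the point: adjustment gains on either reading, and which reading applies is not fixed.

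Further objections that stand:

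- At r = 0.3, against follow-up values, the gain is small (9% of the variance).
- The planned pressure SDs of 250 and 100 differ, so the equal-variance formula is doubtful for that outcome.
- These outcomes are secondary, and pressure is well powered without adjustment.
- Section 2.7 also plans means with SD or medians with interquartile range, so p-values would not be reported alone. These summaries are not a between-arm difference with an interval, however.

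Two stronger readings are tempting, and the article supports neither. A reader might infer that chance baseline imbalance biases the unadjusted result. Randomisation keeps the test valid, and its error rate already allows for such imbalance. A reader might also infer that signed-rank tests within each arm will be offered as evidence that tenotomy works. Section 2.7 does not say so, and its next sentence provides a test between groups.

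**Conclusion.** The point holds as one of efficiency and reporting, not of bias or invalidity. For the continuous secondary outcomes, the single between-arm test named accepts no baseline covariate and yields no effect estimate or interval, while the baseline data are collected anyway.

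The size depends on a correlation the article does not give and on which values are ranked. Over r = 0.3 to 0.7, the adjusted analysis has 0.51 to 0.91 of the variance of a comparison of follow-up values, or 0.65 to 0.85 of that of a comparison of change scores. Even against the better of the two at each r, the reduction is 9%, 25% and 15%. Joint angles and quality of life stand to gain most; the conclusion on pressure is unlikely to depend on it if the planning figures are right.

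**What to change.** In section 2.7, or in the analysis plan with the departure noted, state that the between-arm analysis of barefoot peak pressure, MTPJ/PIPJ/DIPJ angles, SF-36 and EQ-5D-5L is a linear mixed model over the follow-up visits. It should include arm, visit, arm-by-visit and the baseline value of the outcome, with a participant random effect. Report the adjusted between-arm difference with its 95% CI. For pressure, log-transform or allow unequal variances by arm if needed. Keep Kruskal-Wallis as a sensitivity analysis, say whether it ranks follow-up values or changes, and label Wilcoxon signed-rank results as descriptive.

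The cost is wording only. No visit, measurement or participant is added, and SPSS, the package already named, fits these models. The change should be made before the outcome data are analysed.

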### Trial design

2.2

This study concerns a randomized controlled trial (RCT) with a 24-month follow-up period at the out-patient clinic (Table 1). Sixty-six participants will be included. Inclusion started in March 2022. After informed consent is signed, participants are randomized into two groups: usual care (control) or usual care plus flexor tenotomy (intervention). The researchers analyzing the effect of the data will be blinded for group allocation. The treating physician, orthopedic surgeon and participant will not be blinded to group allocation. The flexor tenotomy will be an addition to usual care and is scheduled after randomization. This means that the intervention group will receive the same standard care as the control group including orthopedic shoes.

**Table 1 tbl1:** Standard protocol items.

**Time point**	Study period						
	Enrolment	Allocation	Post-allocation				Close-out
	−2 weeks	−1 week	0	1 week	6 months	12 months	24 months
Enrolment							
Initial eligibility screen	X						
Study information to participant	X						
Initial willingness to participate		X					
Crosscheck inclusion/exclusion criteria		X					
Informed consent			X				
Final eligibility screen			X				
Allocation			X				

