#### Ulcer recurrence

2.5.1

The main study outcome is ulcer recurrence on the treated toe within 2 years of follow-up. Transfer ulcers on the adjacent toes, or metatarsal heads within 2 years of follow-up will also be recorded. The formation of a claw or hammer toe in the adjacent toes will be recorded as a complication. Ulcers are defined according to the IWGDF-guideline [26]. Participants are regularly checked for ulceration by the treating physicians of the out-patient clinic or by their podiatrist.

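### Cheap improvement: the 2-year recurrence outcome is paired with Fisher's exact test, which cannot use the follow-up of participants who withdraw ulcer-free; a time-to-event primary analysis can

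*Protocol article*

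**What the plan says.** - **Outcome** (section 2.5.1, Ulcer recurrence): "The main study outcome is ulcer recurrence on the treated toe within 2 years of follow-up".
- **Follow-up** (section 2.2, Trial design): "This study concerns a randomized controlled trial (RCT) with a 24-month follow-up period at the out-patient clinic".
- **Ascertainment** (section 2.5.1): "Participants are regularly checked for ulceration by the treating physicians of the out-patient clinic or by their podiatrist". Table 1 also schedules an ulcer assessment at baseline, 1 week, and 6, 12 and 24 months.
- **Between-group test** (section 2.7, Statistical analysis): "Differences between groups will be compared using Fisher's Exact test or Kruskal-Wallis", and "A level of p < 0.05 is considered statistically significant". Neither test is tied by name to the primary outcome. No Kaplan-Meier, log-rank, Cox or person-time analysis is named.
- **Sizing** (section 2.6, Sample size calculation): "we estimate 8% recurrence in 12 months in the intervention group"; "In the control group, we estimate 36% ulcer recurrence in 12 months"; "power 0.8, alpha 0.05, 1:1 randomization and intention-to-treat analysis, a total of 66 participants (33 per group) are required". No allowance for loss to follow-up is stated.

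**The concern.** Recurrence accumulates over two years, and some participants can be expected to leave before the end. A 2x2 table has a place only for people whose 24-month status is known. Someone who withdraws at month 15 without an ulcer has given 15 months of information, but the table either records a full 24 ulcer-free months or discards the person.

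The first choice pulls the risk in that arm down and the second pushes it up. The treatment difference moves accordingly. If the arms lose people at different rates, a difference can appear where there is none. Participants and treating physicians know the allocation (section 2.2), so unequal loss is plausible, although the article does not predict it.

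Two kinds of early exit are not part of this problem. A loss after the first ulcer leaves the outcome known. A death without an ulcer is a competing event, not a missing outcome.

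**Working it through.** **1. The plan's own figure.** Inputs from section 2.6: 36% v 8% at 12 months, power 0.80, alpha 0.05 (two-sided assumed), 1:1. With pooled p = 0.22:

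n per arm = [1.96·√(2·0.22·0.78) + 0.842·√(0.36·0.64 + 0.08·0.92)]² / 0.28² = 33.15.

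Rounded to the nearest integer this gives the stated 33 per arm, 66 in total. It is a two-proportion calculation without continuity correction.

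**2. 24-month risks without loss.** Assumption: the 12-month hazard stays constant.

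- Control: 1 − 0.64² = 59.0%
- Intervention: 1 − 0.92² = 15.4%
- Difference: 43.7 points; hazard ratio ln 0.92 / ln 0.64 = 0.187

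**3. What a 2x2 table would show with ulcer-free loss.** Assumption: loss is independent and exponential, with rate m per year and proportion R retained at 24 months, so m = −ln(R)/2. Let h be the ulcer hazard (−ln 0.64 = 0.446; −ln 0.92 = 0.083) and K = (12-month ulcer-free proportion)² × R, the proportion still followed and ulcer-free at 24 months.

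- Lost counted ulcer-free: A = h/(h + m) × (1 − K)
- Lost dropped: A/(A + K)

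Example, control arm, R = 0.80: m = 0.112, K = 0.4096 × 0.80 = 0.328, A = 0.446/0.558 × 0.672 = 53.8%. With the lost dropped: 0.538/(0.538 + 0.328) = 62.1%.

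| Loss per arm | Handling | Control | Intervention | Difference |
|---|---|---|---|---|
| None | – | 59.0% | 15.4% | 43.7 |
| 20% over 24 months | counted ulcer-free | 53.8% | 13.8% | 40.0 |
| 20% over 24 months | dropped | 62.1% | 16.9% | 45.2 |
| 15% per year (R = 0.85² = 0.7225) | counted ulcer-free | 51.6% | 13.2% | 38.4 |
| 15% per year | dropped | 63.6% | 17.7% | 45.8 |

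A simulation of 5,000 trials at 20% loss gave differences of 40.2 and 45.5, in line with the formula.

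**4. Unequal loss with no true effect.** Both arms have a true risk of 59.0%; loss is 10% in one and 30% in the other. The same formulas give 56.5% v 51.0% (counted ulcer-free) or 60.5% v 64.0% (dropped), which are false gaps of 5.5 and 3.5 points in opposite directions. At 33 per arm the simulated rejection rate of Fisher's test stayed near or below nominal (0.053 and 0.036), so the harm is to the estimate more than to the error rate.

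**5. Power at the extrapolated 24-month risks, 33 per arm (simulated).**

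| Loss over 24 months | Fisher, lost = no ulcer | Fisher, lost dropped | Log-rank |
|---|---|---|---|
| 0% | 0.954 | 0.954 | 0.973 |
| 10% both | 0.940 | 0.948 | 0.970 |
| 20% both | 0.924 | 0.930 | 0.961 |
| 30% both | 0.892 | 0.909 | 0.948 |
| 30% control, 10% intervention | 0.857 | 0.961 | 0.961 |
| 10% control, 30% intervention | 0.959 | 0.887 | 0.958 |

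With complete follow-up, an uncorrected chi-square test has 0.975 power by exact enumeration, the same as log-rank. The no-loss gap is therefore Fisher's conservatism and does not come from ignoring time. The same holds at the 12-month rates: Fisher 0.730, chi-square 0.826, log-rank 0.824.

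**The case against.** A yes/no outcome at a fixed horizon, compared by a two-proportion test, is coherent and matches how the trial was sized. The article states intention-to-treat. How losses are handled is commonly left to a full protocol or statistical analysis plan, and imputation would be a third route for a 2x2 table. The size of the bias therefore rests on handling and loss rates that the article does not give. All of this stands, and it is why the point is an improvement and not the correction of an error. It does not remove the limitation: whatever is decided about losses, Fisher's test still needs a 24-month status for every participant.

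A reader might infer three stronger things that the documents do not support:

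- **That every death or loss biases the result.** Exits after a first ulcer do not. Under a cumulative incidence estimand, a participant who dies ulcer-free is correctly counted as having had no ulcer.
- **That substantial power is thrown away.** In every loss scenario tried, Fisher's test keeps about 86 to 96% power at the extrapolated 24-month risks. A larger gap can be produced by assuming a lower control risk, but section 2.6 plans on 36% and cites 40%.
- **That exact onset dates are already in hand.** The article describes regular checks and scheduled assessments. It does not say that the date of each ulcer is recorded.

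**Conclusion.** The point holds as a cheap improvement. The only listed between-group test that fits the main outcome cannot use the follow-up of participants who withdraw ulcer-free, and the two simple ways of placing them in a 2x2 table move the risk difference in opposite directions. From a true 43.7 points it shifts to about 40 or 45 at 20% loss over 24 months, and to 38.4 or 45.8 at 15% loss per year. Unequal loss can produce a false gap of a few points.

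The power gain is secondary: about 2 points with no loss, and about 2 to 6 points with equal loss of 10 to 30%.

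These sizes assume constant hazards beyond 12 months, independent loss, known ulcer dates and a two-sided 5% level. The loss rates are illustrative, since the article gives none.

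**What to change.** In section 2.7, and in the analysis plan before any comparison by arm:

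1. Make the primary analysis time from randomisation to first ulcer on a toe indicated for tenotomy at baseline, with the same definition in both arms. Compare arms by a two-sided log-rank test, with a cause-specific Cox hazard ratio and 95% CI.
2. Censor ulcer-free withdrawals at the last foot check.
3. Report one absolute estimand: the difference in 24-month cumulative incidence with 95% CI, with death and amputation of that toe as competing events. Do not add a Kaplan-Meier risk difference that censors deaths, because it answers a different question.
4. Keep the 24-month Fisher test as a sensitivity analysis, with its handling of losses stated.
5. Record the date of each first ulcer and of the last foot check.

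**Cost.** Analysis wording and two date fields; no extra participants or visits. The downside is that onset dates are only as exact as the checks. The last scheduled interval runs from 12 to 24 months with only routine checks between, and check frequency could differ by arm. Report that frequency by arm and add an interval-censored sensitivity analysis.

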## Conclusion

3

This protocol describes a randomized controlled trial exploring the efficacy of percutaneous needle flexor tenotomy to prevent recurrent ulceration. The study will assess clinical outcomes as well as biomechanical and anatomical changes of the toes and cost-effectiveness. This will provide a comprehensive analysis of the effects of this operation. The results of the DIAFLEX trial is expected support the implementation of needle flexor tenotomy in diabetic foot care.

## Data Availability

No data was used for the research described in the article.
